### Assignment of interventions

#### Sample size calculation

A total of 48 breastfeeding HIV exposed uninfected eligible neonates will be enrolled in the study (8 neonates recruited in each arm). Power calculations were not performed for this study, given that it is a Phase 1 trial aiming to test safety and PK in a small number of participants [12]. The trial objectives specifically state an evaluation of safety that did not include comparing safety between arms; thus there was no need to perform power calculation. We have, however, carefully evaluate and presented the probability of observing at least one event under various hypothetical SAE rates and this forms the key sample size consideration. The enrolment of 48 neonates will allow the study to have 8 infants per arm (target sample size of each arm is 6) in the final safety dataset in the hypothesis of a 25% of lost to follow-up.

The probabilities reported in Table 6 highlight the likelihood of the study to detect either rare or common SAEs (Table 6). According to the reported probabilities, there is 11% chance of getting 2 SAEs in a sample of 8 participants when the true SAE proportion is 50% (i.e. common) and 5% when the true SAE proportion is 5% (i.e. rare). In addition, there is 0.4% chance of getting 0 (no) SAEs in a sample of 8 participants when the true SAE proportion is 50% (i.e. common) and 66% when the true SAE proportion is 5% (i.e. rare).

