#### Primary analysis on primary endpoint

The primary endpoint of each step is the proportion of neonates who develop at least one ≥ 1 Grade 3 adverse events (AE) possibly, probably or definitely related to each bNAb that occurred within 28 days after a first or a second dose of bNAbs administration (alone or in combination). The primary endpoint will be described according to the study arm, using proportions with the corresponding 95% CI.

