#### Missing data/loss to follow-up

All reasonable efforts will be taken to minimise loss to follow-up, which is expected to be minimal as data collection for primary and secondary endpoints. Contact details recording and tracking systems are in place to ensure a low rate of lost in the study; in addition, in the sample size calculation, we allowed for a 25% of loss to follow‐up. The number and percentage of participants with complete follow-up information at day 28 and at 6 months, since first or second dose of bNAbs administration (alone or in combination), will be reported.

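### The sample size text swaps recruited and evaluable numbers: 8 per arm less 25% loss is 6, and the quoted event probabilities hold only for 8

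*Protocol article*

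**What the plan says.** Under Sample size calculation, the protocol article states: "A total of 48 breastfeeding HIV exposed uninfected eligible neonates will be enrolled in the study", with "8 neonates recruited in each arm". It then says that this enrolment "will allow the study to have 8 infants per arm (target sample size of each arm is 6) in the final safety dataset". The assumption attached to that sentence is that a quarter of the infants are lost. The section Missing data/loss to follow-up repeats the allowance ("in the sample size calculation, we allowed for a 25% of loss") but also says: "All reasonable efforts will be taken to minimise loss to follow-up, which is expected to be minimal".

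No power calculation was made. The article instead presents the chance of seeing events under hypothetical rates as its main sample size consideration. It quotes four figures for a sample of 8: for 2 SAEs, 11% at a true rate of 50% and 5% at a true rate of 5%; for no SAEs, 0.4% and 66% at the same rates.

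Under Statistical methods, the safety dataset consists of dosed infants who either had a grade 3–4 SAE within 28 days of a dose or completed the 28 days with safety assessment. The primary output is per arm: "The primary endpoint will be described according to the study arm, using proportions with the corresponding 95% CI". The exact method is specified for these intervals.

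**The concern.** One sentence gives two per-arm sizes and attaches the larger to the final dataset after loss. Eight recruited infants cannot remain eight after a quarter are lost.

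The four probabilities all rest on 8, and in a trial without a power calculation they are the sizing argument. If loss reaches the planned level, the chance of missing a toxicity altogether is higher than stated, and an arm with no events supports a weaker safety statement than a reader would take from the text. The probabilities are also worded for SAEs, whereas the primary endpoint is a Grade 3 or higher AE at least possibly related to the bNAb, so the text does not link them to the event that will be analysed.

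**Working it through.** **Inputs.** From Sample size calculation: 48 enrolled, 8 per arm, target 6 per arm, 25% loss, true rates of 5% and 50%. Table 1 gives six separate cohorts of 8; arm 6b re-uses the arm 6 infants.

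**Step 1, the sizing.**
- Recruited number: target/(1 − loss) = 6/0.75 = 8 per arm, and 6 × 8 = 48. The plan's recruitment figure reproduces.
- Evaluable number: 8 × 0.75 = 6 per arm, and 48 × 0.75 = 36. Only the bracketed 6 fits the final dataset under 25% loss.

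**Step 2, the quoted probabilities.** Formula: P(X = x) = C(n, x) pˣ (1 − p)ⁿ⁻ˣ.

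At n = 8:
- 2 events, p = 0.5: 28/256 = 10.9% (stated 11%)
- 2 events, p = 0.05: 28 × 0.05² × 0.95⁶ = 5.1% (stated 5%)
- 0 events, p = 0.5: 1/256 = 0.39% (stated 0.4%)
- 0 events, p = 0.05: 0.95⁸ = 66.3% (stated 66%)

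All four reproduce.

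At n = 6:
- 2 events, p = 0.5: 15/64 = 23.4%
- 2 events, p = 0.05: 15 × 0.05² × 0.95⁴ = 3.1%
- 0 events, p = 0.5: 1/64 = 1.6%
- 0 events, p = 0.05: 0.95⁶ = 73.5%

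None matches the quoted value. The first figure rises because it is the chance of exactly 2 events. It is not a measure of detection.

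**Step 3, what this does to detection.**

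| Quantity | n = 8 | n = 6 |
|---|---|---|
| P(at least 1), p = 5% | 33.7% | 26.5% |
| P(at least 1), p = 10% | 57.0% | 46.9% |
| P(at least 2), p = 20% | 49.7% | 34.5% |

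**Step 4, an arm with no events.** The exact two-sided 95% upper limit is 1 − 0.025^(1/n).
- n = 8: 1 − 0.025^(1/8) = 36.9%
- n = 6: 1 − 0.025^(1/6) = 45.9%

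**The case against.** The strongest reply is that this is a slip of wording with no effect on the design. The sentence itself names 6 as the target, and 6/0.75 gives the recruitment number. The article defines enrolled as having received study product, so 8 infants per arm are dosed. The pause rule under Analyses and stopping rules counts events among eight infants, and the probabilities are openly labelled as being for 8 participants. Loss is expected to be minimal. The 25% is not tied to day 28, so an infant lost at month 4 after one dose would still be in the 28-day safety dataset. An infant with a grade 3–4 SAE within 28 days stays in even if lost afterwards.

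Most of this stands. A reader might infer that the trial is under-enrolled, or that only 6 per arm will be analysed whatever happens. The documents support neither. Six is the planned-loss case and 8 the no-loss case. Because infants with qualifying SAEs are kept, a plain binomial at n = 6 may somewhat understate detection of those events. That protection is partial, however: it depends on the event being an SAE, while the primary endpoint is a related Grade 3 or higher AE, serious or not.

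A reader might also infer that every probability in the plan rests on 8. Table 6 is not shown, so this cannot be checked. The 38% ceiling stated after Table 6 for at least one SAE is a separate matter. It matches exactly one event at n = 8 and a 10% rate (38.3%), whereas at least one event there has probability 57.0%. Changing n does not repair it.

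Finally, naming the primary endpoint event in place of SAEs changes no binomial value, since these depend only on the rate and n. It is a matter of labelling.

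**Conclusion.** The concern holds in a limited form. The statement that 8 per arm remain in the final safety dataset after 25% loss is arithmetically impossible; recruited and evaluable numbers have been swapped. The recruitment number is right and no sizing error follows.

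The four quoted probabilities describe the no-loss case only. At the plan's own evaluable target, the chance of seeing no event at a true 5% rate is 73.5% rather than 66.3%, and the zero-event upper limit rises by 9 percentage points, from 36.9% to 45.9%.

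These figures assume independent events with a common rate within an arm, loss unrelated to events, and, for n = 6, that the full 25% is lost before day 28. The article does not say how much of the loss falls that early, so the actual position lies between the two columns if loss does not exceed 25%.

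Severity is minor to moderate. The analysis is descriptive and its exact intervals will reflect the actual denominator, but the misstatement sits in the trial's only sample size rationale.

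**What to change.** - Restate the sentence along these lines: 8 infants enrolled and dosed per arm (48 in total); 6 per arm (36 in total) evaluable in the final safety dataset if 25% are lost to follow-up.
- Give the event probabilities at n = 6 beside those at n = 8, in the text and, if it lacks them, in Table 6.
- State that the probabilities apply to the primary endpoint event, a related Grade 3 or higher AE.

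The cost is a change to one paragraph and, if needed, one table. No extra infants and no change to the analysis or the pause rule are involved. The price is that the stated figures become slightly less favourable.

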**Table 6 Tab6:**
[figure not shown]
Binomial probabilities of detecting SAEs at hypothetical true event rate

The chances to pause the study are rather low since the probability to observe at least 1 SAE is at most 38%. A larger sample size would increase this probability but this would imply exposing a greater number of infants to the experimental drug.

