#### Analyses and stopping rules

Stopping rules have been defined and will be applied in order to protect the study participants from unnecessary exposure to the monoclonal antibody, should the safety profile prove unacceptable in this population. Unblinded interim exploratory (as this trial is proof-of-concept, no flexible alpha spending function approach will be employed) analyses are planned when the last infant of each study arm will have completed 28 days of follow-up since the first dose of bNAb(s) (individually administered or in combination). These analyses may lead to stop enrolment of subsequent dose arms, adjustment of doses or of the second bNAbs administration.

If at any time during the study, the following triggers are met:i)any of the infants dies or has a life-threatening adverse event or any Grade 4 event that is possibly, probably or definitely related to CAP256V2LS or VRC07-523LS administration;ii)two or more of the eight infants in each arm of the study have a Grade ≥ 3 adverse event at least possibly related to CAP256V2LS or VRC07-523LS administration (excluding Grade 3 neutropenia and anemia, and hyperbilirubinemia), the study investigators will pause the study for evaluation and will request that a DSMB review be performed within 7 days since the event occurrence. The DSMB will decide what additional data they would like to see and advise the study investigators on how to proceed. DSMB may decide on premature termination of some dose/arms (not of the trial); the decision may apply to either the CAP256V2LS or the VRC07-523LS arms (to each single dose/arm) and considers the occurrence in the CAP256V2LS arms independent of that in the VRC07-523LS arms. If the DSMB decides that further enrolment or administration cannot be continued, the study will stop accrual or administration but continue safety follow-up of all enrolled infants.

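### The stated ceiling of 38% on the chance of at least one SAE contradicts the plan's own zero-event probabilities, so the inference that a pause is unlikely is unsupported

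*Protocol article*

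**What the plan says.** Sample size calculation sets the design: "A total of 48 breastfeeding HIV exposed uninfected eligible neonates will be enrolled in the study (8 neonates recruited in each arm"). It does no power calculation. Instead it says the authors "presented the probability of observing at least one event under various hypothetical SAE rates", and calls this the key consideration for sample size.

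Four probabilities for 8 infants follow. For two SAEs, "there is 11% chance of getting 2 SAEs in a sample of 8 participants when the true SAE proportion is 50" per cent, against 5% when the true proportion is 5%. For none, "there is 0.4% chance of getting 0 (no) SAEs in a sample of 8 participants when the true SAE proportion is 50" per cent, against 66% when the true proportion is 5%.

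The text after Table 6 then concludes: "The chances to pause the study are rather low since the probability to observe at least 1 SAE is at most 38" per cent. It adds that a larger sample would raise this probability, at the price of exposing more infants.

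The pause rules are under Analyses and stopping rules. One trigger needs a single death, life-threatening event or related Grade 4 event. The other applies when "two or more of the eight infants in each arm of the study have a" Grade 3 or higher event at least possibly related to product, with some Grade 3 laboratory events excluded. Separately, Study design and Toxicity management and enrolment in study arms make progression to later arms depend on seeing no SAE (in Study design, none at least possibly related).

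**The concern.** The chance of at least one event and the chance of no event must add to one. A 0.4% chance of none at a 50% true rate cannot stand beside a ceiling of 38% on at least one.

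The sentence matters because it carries two conclusions: that pauses are unlikely, and that 8 per arm is a sensible trade-off against exposing more infants. Both rest on the quantity that the plan itself names as key. A reader who takes 38% at face value would underestimate how readily 8 infants reveal a common toxicity, and could be too confident that the trial will run without a pause.

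**Working it through.** **Inputs.** n = 8 per arm and 48 in total; true rates of 5% and 50%; stated probabilities 0.4%, 66%, 11% and 5% (all from Sample size calculation). Disputed figure: 38% (text after Table 6). Trigger threshold: two or more of eight (Analyses and stopping rules). The 1%, 10% and 20% rates below are added for illustration.

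**Step 1: reproduce the plan's four figures.** With P(X = x) = C(8, x) p^x (1 − p)^(8 − x):
- p = 0.50: P(0) = 0.5^8 = 0.0039; P(2) = 28 × 0.5^8 = 0.109.
- p = 0.05: P(0) = 0.95^8 = 0.663; P(2) = 28 × 0.05² × 0.95^6 = 0.051.

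All four reproduce as point probabilities for n = 8.

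**Step 2: chance of at least one, from the plan's own figures.**
- 50% rate: 1 − 0.004 = 0.996.
- 5% rate: 1 − 0.66 = 0.34.

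**Step 3: where the 38% ceiling would hold.** Solving 1 − (1 − p)^8 = 0.38 gives p = 1 − 0.62^(1/8) = 0.058. Above a true rate of about 5.8% the ceiling is broken. Using 6 evaluable infants does not rescue it: the limit becomes 1 − 0.62^(1/6) = 0.077, and at a 50% rate the chance is still 1 − 0.5^6 = 0.984.

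**Step 4: likely source of 38%.** P(exactly 1 of 8) = 8p(1 − p)^7. This is 0.383 at 10% and 0.385 at 15%. Its maximum, at p = 1/8, is (7/8)^7 = 0.393. That fits both the number and the words "at most". One other match exists: P(at least 1 of 48) at a 1% rate is also 0.383, but that cannot be a maximum over a range that includes 5% and 50%.

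**Step 5: per-arm cumulative probabilities, n = 8.** P(≥2) = 1 − P(0) − P(1).

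| True rate | P(exactly 1) | P(≥1) | P(≥2) |
|---|---|---|---|
| 5% | 27.9% | 33.7% | 5.7% |
| 10% | 38.3% | 57.0% | 18.7% |
| 20% | 33.6% | 83.2% | 49.7% |
| 50% | 3.1% | 99.6% | 96.5% |

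The plan's 11% and 5% are exactly-two values. The corresponding two-or-more values are 96.5% and 5.7%.

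**Step 6: across the trial (illustration).** The chance that any of six groups of 8 reaches two or more is 1 − (1 − P(≥2))^6:
- 1% rate: 1 − (1 − 0.0027)^6 = about 1.6%.
- 5% rate: 1 − (1 − 0.0572)^6 = 29.8%.
- 10% rate: 1 − (1 − 0.1869)^6 = 71.1%.

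For a trigger that needs one qualifying event in any of 48 infants, 1 − (1 − p)^48 is 38.3% at a 1% rate of such events and 91.5% at 5%.

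These trial-wide values assume independent infants and equal rates. The six-group values count one observation window per infant and ignore the exclusions in the two-or-more trigger.

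**The case against.** The best defence is that the sentence is a slip in one label, that the other quoted probabilities are right, and that nothing operational depends on it. Much of this stands. The 11% and 5% are correct and correctly described as the chance of getting two SAEs, and the plan does not tie them to the pause trigger. The contrast of 0.4% with 66% does show the reader that 8 infants detect common events far better than rare ones. The pause triggers run on event counts, not on these probabilities.

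The defence does not save the 38% sentence. Its remark that a larger sample would raise the probability is always true of at least one event but not of exactly one, so the text means at least one, and the number is wrong for that.

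Several stronger readings are tempting, and the documents do not support them:
- **That a pause is in fact likely.** This depends on the unknown rate of related, graded events. At a 1% rate, the chance that any group reaches two or more is only about 1.6%.
- **That 38% is certainly the exactly-one value.** The fit is close, but the contents of Table 6 are not shown.
- **That these probabilities are the only basis for 8 per arm.** The plan also cites the Phase 1 setting, limited infant exposure, and a "target sample size of each arm is 6" "in the hypothesis of a 25% of lost to follow-up".
- **That the DSMB is misinformed.** Nothing says that it receives these figures.
- **That SAE is simply the wrong event.** Progression between arms is itself conditioned on SAEs, so the chance of at least one SAE is relevant there.

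**Conclusion.** The point holds for the 38% sentence and the inference drawn from it. Over the plan's own range of true rates, 5% to 50%, the chance of at least one SAE in an arm of 8 runs from 34% to 99.6%. The ceiling of 38% is right only at or below a true rate of about 5.8%. This part needs only the binomial model that the plan already uses, and follows from its own figures by subtraction.

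The reassurance about pausing is unsupported, not refuted. The reason given is wrong, and the events that trigger a pause differ from any SAE. The exactly-two probabilities are accurate but do not describe a two-or-more rule. The trial-wide figures of about 30% and 71% show how the chance grows over six groups; they are not estimates of the actual chance of a pause.

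**What to change.** 1. Delete the 38% sentence, or replace it with the chance of at least one SAE per arm of 8: about 34%, 57%, 83% and 99.6% at true rates of 5%, 10%, 20% and 50%.
2. Beside it, give the chance of two or more per arm: 5.7%, 18.7%, 49.7% and 96.5% at the same rates. If Table 6 already holds cumulative values, cite them; if not, add them and label point and cumulative probabilities clearly.
3. Base any statement about pausing on the triggers under Analyses and stopping rules, across all arms, with assumptions stated. An example is about 30% at a 5% rate and 71% at a 10% rate that any of six groups reaches two or more, for independent infants with equal rates and ignoring the trigger's exclusions.
4. Keep the chance of at least one SAE for the SAE-based progression conditions in Study design and in Toxicity management and enrolment in study arms.

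The cost is a few sentences and possibly extra columns in one table. Sample size, triggers and conduct stay as they are. The one downside is that the stated figure is less reassuring.

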#### Randomization and blinding

In arm 1 and 6/6b neonates exposed to HIV and born negative will be sequentially recruited, while in arms 2 or 4 and arms 3 or 5 further exposed neonates without HIV will be allocated in a ratio 1:1 using a randomization list that will be computer-generated by the trial statistician and provided through a paper-based envelope approach. The randomization list will be stratified in permuted block of size of 4; it will be used in step 1 (arms 2 to 5 only).

The trial is single-blind with neonates’ mothers blinded with respect to study product allocation to minimize the potential of contamination between arms (mothers allocated to one bNAb study product and willing to change to benefit from the other bNAb) and maximize an objective measurement of the primary outcome. We chose not to design a double-blind trial because doses within groups will be administered in a sequential way; this condition implies that even if the study staff does not know the exact dose administered, they will still be able to guess that the doses gradually administered are in increasing quantities, and, thus, eliminating at least in part the advantage of the double-blind design.

### Data collection, management and analysis

#### Data collection methods

Data will be collected for each subject in case report forms (CRFs) that will be electronic (eCRFs) and available through REDCap application version 9.3.5 (Vanderbilt University, Nashville, USA). The data will be entered directly into the REDCap server (https://samrc-redcap.mrc.ac.za) using tablets. Paper CRFs will be available as backup.

Data will be reviewed and checked for completeness and validity before, during and after data entry. The data cleaning process will include different levels of controls: (a) Source data verification and quality checks at data entry level; (b) Automatic controls on the REDCap database; (c) Database data review performed by the data manager, with the production of manual eQueries.

Entered data will be subject to visual and electronic validation by data management and monitoring staff. Any errors, inconsistencies and unexpected values in the data will be noted and queried with site staff for resolution.

Adverse events and Medical History will be coded using the Division of AIDS Table for Grading the Severity of Adult and Paediatric Adverse Events, Corrected Version 2.1, July 2017. Concomitant Medications will be coded using the World Health Organization Drug Dictionary (WHO-DDE Dictionary), the last available version.

The collected clinical data will be coded into standard medical terminology according to the International Conference on Harmonisation of Technical Requirements for Registration of Pharmaceuticals for Human Use Multidisciplinary guidelines (ICH M1).

When data review is finalised, the database will be ready for statistical analysis.

#### Data management, storage and curating data

Data management activities will be undertaken under the applicable regulatory frameworks and data management standard processes are aligned with the Good Clinical Data Management Processes (GCDMP). A governance structure will be established to oversee the development process, coordinate relevant stakeholders, facilitate decision making, advocate for resources, provide accountability for data security, and mandate the study implementation. Further, the governance structure will ensure that the study adheres to national health data policies. The SAMRC will develop and host the REDCap database. Infrastructure: Online hosting service; tablets with keyboards for data collection and linked to the central server; connectivity in facilities; centralised server/software instance model. Source documents: All the original documents for each participant in the study will be stored securely. Every effort will be made to anonymise (assigning codes and/or pseudonyms) data and protect individual confidentiality in analysis, synthesis, and dissemination activities. Original CRFs and supporting documentation regarding corrections and data changes will be digitalised. All CRFs will be assigned a unique identifier code (UIC) during data entry into the database. Mother-infant dyads will be linked using UIC. No source documents will be destroyed without permission in writing from the SAMRC. All laptops and tablets will have secure usernames and passwords. Data backup: Automated, scheduled data backups in real-time will be stored on a virtual server. We will also develop a standard operating procedure for disaster recovery planning. Given the sensitivity of mother-infant data, any backups and disaster recovery measures must be just as secure as the data in the production instance. Backups will be encrypted to the same standard as the database instance.

